## Assignment of interventions: blinding

### Who will be blinded {17a}

Care will be taken not to inform participants of treatment group assignment, except where necessary for patient safety (e.g. allergic reaction). Research delivery staff assessing participant outcomes will be masked to treatment group assignment wherever possible. However, complete blinding of all clinicians and research staff is not feasible, and IMP administered will be recorded in the clinical notes according to usual clinical care.

During the trial, the Trial Management Group and the Trial Steering Committee will not see outcome results broken down by treatment arm.

### Procedure for unblinding if needed {17b}

The clinical team will not be blinded to the IMP administered, and this will be recorded in the clinical notes, so there will be no specific unblinding procedure.

## Data collection and management

### Plans for assessment and collection of outcomes {18a}

Baseline, perioperative, and outcome data will be collected by trained site research staff from medical notes using an electronic or paper case report form (CRF). Baseline EQ-5D-5L questionnaires (available from www.euroqol.org) will be completed by face-to-face or telephone interview prior to surgery, or if necessary (e.g. in the case of emergency surgery), by retrospective completion at the earliest opportunity post-operatively. QoR-15 questionnaires [31] will be completed face-to-face by a member of the site research team on post-operative day 1.

Day 30 follow up for hospital readmission and mortality will be completed by review of medical records, and if necessary, by telephone contact by site research staff with the participant or their General Practitioner. Participants will be contacted by telephone and/or email at 30 days post-surgery (or as close as possible) and again at 180 days (or as close as possible) by site research staff. During these contacts, data on health resource use will be collected, and quality of life will be assessed using the EQ-5D-5L questionnaire. If patients are physically unable to complete the EQ-5D-5L questionnaire, this can be completed by a member of the research team or a carer on their behalf.

## Allergic sensitisation substudy

### Baseline blood sampling and processing

Where possible, 10 mL of blood will be taken following induction of anaesthesia and prior to the administration of the IMP (either pre- or post-randomisation). Where this is not possible, the blood sample will be taken as close as possible to IMP administration. The samples will be processed in the hospital laboratory, frozen, and stored. Samples will be transported in batches to the immunology laboratory at Leeds Teaching Hospitals NHS Trust, at a time of mutual convenience, where mast cell activation testing will be performed. Any samples not used will be disposed of in accordance with local policy and applicable regulations.

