#### Crossover

Due to more rapid onset of action with sugammadex than neostigmine, and ability to reverse more profound degrees of neuromuscular blockade, the risk of crossover is greatest from neostigmine to sugammadex. Possible scenarios include the presence of deep neuromuscular blockade at the end of surgery, for example if surgery is completed more quickly than expected or a larger dose of neuromuscular blocking drug is given towards the end of the case.

Strategies to ensure eligibility and avoid crossover therefore include (a) encouraging, though not mandating, that randomisation occurs close to the timepoint when neuromuscular reversal is given, i.e. as late as possible, (b) encouraging clear communication between research delivery teams and treating anaesthetists to ensure eligibility for the trial is confirmed as close as possible to the time of randomisation, and (c) providing written guidance to anaesthetists to remind them of national guidelines supporting the routine use of quantitative neuromuscular monitoring to guide dosing of neuromuscular blocking drugs and reversal agents. These measures are intended to minimise the risk of a trial participant being randomised but not receiving a reversal agent.

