### Follow-up testing at 6 weeks to 6 months

Following baseline blood sampling, and depending on group allocation, participants will undergo a clinical assessment, comprising review of notes and/or telephone or face-to-face consultation by an allergy specialist. This assessment will determine suitability for skin testing. Participants will be asked to attend a local drug allergy clinic between 6 weeks and 6 months after their surgery for repeat blood sampling (for mast cell activation) and, if appropriate, a skin test. In line with routine drug allergy skin testing clinics, some medications may be discontinued for a period of one week prior to testing. Where appropriate in the clinical judgment of the allergy specialist, skin testing will be performed at an allergy clinic. This comprises skin prick and intradermal testing on the forearm of both arms, each test 2 cm apart. Positive and negative control tests will be performed on the forearm using histamine and saline respectively prior to skin prick testing, to ensure that the patient’s skin is appropriately reactive. A negative control saline intradermal test will be performed prior to intradermal testing, to confirm appropriate skin reactivity. The testing takes around one hour in total and involves minor discomfort from the slight scratching of the skin with each test. Any skin test developing a wheal of 3 mm or greater than the negative control site is usually considered positive, but the result of the test is a clinical judgment of the allergy specialist. Systemic reactions to skin testing are rare but can occur, typically involving urticaria and a sensation of itch, although more severe allergic reactions are possible. The testing will be performed by specialists who are trained and experienced in the conduct and management of skin testing, and who will treat any symptoms which occur in line with local and national guidance. The patient will be contacted between 48 h and one week following testing to check whether any of the test sites developed localised redness or swelling, which indicates a possible delayed-type allergic reaction. In line with standard drug allergy testing procedure, patients may be offered a drug provocation test, whereby they are given small doses of sugammadex in a carefully monitored setting at the earliest practical opportunity. This is both for future safety of the patient and to understand the specificity of skin testing.

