## Plans for collection, laboratory evaluation and storage of biological specimens for genetic or molecular analysis in this trial/future use {33}

In selected study sites, biological samples will be collected which will be stored for future analysis as part of a separate research programme aiming to understand biological phenotypes in the perioperative period. This work will be subject to separate ethical approval and separate funding application(s). With patient consent, 30 mL blood samples (approximately) will be taken on two occasions: at baseline (any time between consent and the beginning of the surgery) and on post-operative day 1 at 12–24 h following the end of surgery or as close as possible. This will be processed according to a specified standard operating procedure. Samples will be transferred in batches, at a time of mutual convenience, to a laboratory at Queen’s University Belfast for analysis and storage for future use. If a patient is enrolled but not randomised, sampling and data collection will proceed unless the patient is specifically withdrawn from the substudy.

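### The fallback for the substudy's baseline mast cell activation sample permits a draw after the study drug, so the only planned pre-exposure measurement may be a post-exposure one

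*Protocol article*

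**What the plan says.** The baseline draw has a preferred time and a fallback, both in Baseline blood sampling and processing. The preferred time is: "Where possible, 10 mL of blood will be taken following induction of anaesthesia and prior to the administration of the IMP". The fallback is: "Where this is not possible, the blood sample will be taken as close as possible to IMP administration". The draw may come before or after randomisation. The blood is then frozen and sent in batches to a central laboratory, "where mast cell activation testing will be performed".

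The second sample belongs to the allergy clinic visit (Follow-up testing at 6 weeks to 6 months), which participants attend "between 6 weeks and 6 months after their surgery for repeat blood sampling (for mast cell activation) and, if appropriate, a skin test". Skin testing belongs to that visit as well: "Where appropriate in the clinical judgment of the allergy specialist, skin testing will be performed at an allergy clinic". Table 1 agrees. It marks mast cell blood at day 0 and at the clinic visit, and skin testing at the clinic visit only.

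For the trial's other blood sample, stored for future research, the article allows a much wider window: "at baseline (any time between consent and the beginning of the surgery".

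**The concern.** The substudy aims to estimate sensitisation after one exposure to sugammadex (Hypothesis and objectives). The eligibility criteria exclude known allergy but not earlier exposure, and the Discussion says that UK use is growing. Some participants may therefore already be sensitised at entry, and only a measurement taken before the trial dose can show it.

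The fallback ranks nearness to the dose above being before the dose. For a pre-exposure measurement the order should be the reverse. A sample drawn shortly after a sugammadex bolus is not a pre-exposure sample, and it may carry the drug whose reactivity is being tested. A sample drawn after neostigmine alone would not. At stake is whether the day-0 result can be read as a baseline, either against the follow-up result in the same person or between the two groups.

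**Working it through.** The article states no figure to reproduce: the substudy has no formal sample size calculation. The check is mainly a reading of the rule against the schedule.

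**1. What the rule allows.**

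| Time of draw | Preferred rule | Fallback |
|---|---|---|
| Before induction | no | yes |
| Induction to study drug | yes | not needed |
| After study drug | no | yes, with no time limit |

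The fallback covers an early draw as well as a late one. But if the drug has been given and no blood has been taken, only the last row is left, and the rule then steers staff to draw at once. The passage does not label such a sample as anything other than baseline.

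**2. Whether another pre-exposure measurement exists.** Table 1 and the follow-up section place skin testing only at the clinic visit, and the second mast cell sample there too. No other test of sensitisation is planned before the dose, so the day-0 sample stands alone.

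**3. Whether a late sample would contain the drug.** Adverse event reporting and harms says that 24 h is more than five half-lives of the study drugs, so the half-life is below 24 / 5 = 4.8 h. Assume one-compartment decay, fraction remaining = 0.5^(t / half-life), and half-lives from 1 h (an assumed lower end) to 4.8 h:

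- at 30 minutes: 0.5^(0.5/1) = 0.71 to 0.5^(0.5/4.8) = 0.93
- at 1 hour: 0.5^(1/1) = 0.50 to 0.5^(1/4.8) = 0.87

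On these assumptions, a sample drawn within the hour after sugammadex would contain it. This says nothing about the effect on the assay.

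**4. Who is affected.** Sample size {14} counts the groups by drug received: 200 sugammadex and 50 neostigmine, up to 250 in all. Late sugammadex baselines = 200 × p, where p is the share drawn after the drug. The article gives no p. As an illustration only, p of 10% to 30% would give 200 × 0.10 = 20 to 200 × 0.30 = 60. The logical range is 0 to 200.

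**5. Which results depend on the sample.** Outcomes {12} defines the sensitisation rate by skin test and challenge test at the follow-up clinic. Mast cell activation is not in that definition; its stated role is correlation with skin and provocation testing. Those tests are done at or after the clinic visit, where a fresh mast cell sample is planned. Statistical methods {20a} describes descriptive summaries, exploratory count regression of positive results and a comparison with rocuronium sensitisation. It states no paired or baseline-adjusted mast cell analysis.

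**The case against.** The strongest reply is that no stated outcome rests on the baseline sample. As step 5 shows, this is right for the sensitisation rate, and DAH-30 is not involved at all. A reader might infer that the fallback biases the headline rate; the article does not support that. What remains is that the substudy collects a baseline and calls the later draw a repeat, so a before-after reading is the natural use of the pair even though none is specified.

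Second, a reader might infer that drug in the sample is known to distort the test. The article does not say which blood fraction is kept or how it is prepared, so interference is possible but not shown. Nor does anything show that antibody status changes within minutes of a dose.

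Third, the preferred window is not especially narrow. It runs from induction to reversal, which is most of a major operation, and may be used before randomisation. The advice that "randomisation occurs close to the timepoint when neuromuscular reversal is given, i.e. as late as possible" shortens it only where a team chooses to wait for allocation. This objection stands, and it suggests that late draws may be uncommon.

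Fourth, it is tempting to say that the problem exists only in the sugammadex arm. That holds by drug received but not strictly by allocation, because the Crossover section recognises a risk of crossover, greatest from neostigmine to sugammadex.

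Fifth, a baseline drawn during an anaphylactic reaction is a remote prospect. On the rates in Sugammadex and allergy, 200 exposures give 200 / 64,000 = 0.003 to 200 / 5,000 = 0.04 expected cases, even before a missed draw is required.

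Last, sample-time recording and the handling of late samples may sit in the full protocol or a laboratory procedure. Their absence from an article is no fault. The fallback sentence itself is printed, however, and permits a post-drug baseline.

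**Conclusion.** The point holds as a minor defect in the substudy. The fallback permits the baseline mast cell activation sample to be drawn after the study drug, although it is the only planned measurement of sensitisation before exposure. In a participant who received sugammadex, such a sample is post-exposure and may contain the drug under test.

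The effect is limited to the mast cell baseline and to any before-after or between-group reading of it. How many samples are affected cannot be known from the article, and neither can the effect on the assay. The conclusion rests on the wording and the schedule alone; the 20 to 60 illustration and the decay figures are not needed for it.

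**What to change.** Replace the fallback sentence with:

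> The baseline sample is drawn at any time after consent and before IMP administration. The draw time relative to the IMP is recorded. Any sample drawn after the IMP is flagged and is not treated as a pre-exposure baseline; a sensitivity analysis may include it.

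Table 1 would need a matching mark in the baseline column for substudy blood. An early draw should be workable, since the other baseline sample may already be taken at any point from consent until surgery begins.

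The cost is one sentence in the protocol and the laboratory instructions, with no extra visit, procedure or blood volume. The small downside is that a few participants will have no valid baseline. Recruitment was expected to finish by the end of 2025. If sampling is already complete, the flagging can still be applied wherever draw and drug times were recorded.

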### Follow-up testing at 6 weeks to 6 months

Following baseline blood sampling, and depending on group allocation, participants will undergo a clinical assessment, comprising review of notes and/or telephone or face-to-face consultation by an allergy specialist. This assessment will determine suitability for skin testing. Participants will be asked to attend a local drug allergy clinic between 6 weeks and 6 months after their surgery for repeat blood sampling (for mast cell activation) and, if appropriate, a skin test. In line with routine drug allergy skin testing clinics, some medications may be discontinued for a period of one week prior to testing. Where appropriate in the clinical judgment of the allergy specialist, skin testing will be performed at an allergy clinic. This comprises skin prick and intradermal testing on the forearm of both arms, each test 2 cm apart. Positive and negative control tests will be performed on the forearm using histamine and saline respectively prior to skin prick testing, to ensure that the patient’s skin is appropriately reactive. A negative control saline intradermal test will be performed prior to intradermal testing, to confirm appropriate skin reactivity. The testing takes around one hour in total and involves minor discomfort from the slight scratching of the skin with each test. Any skin test developing a wheal of 3 mm or greater than the negative control site is usually considered positive, but the result of the test is a clinical judgment of the allergy specialist. Systemic reactions to skin testing are rare but can occur, typically involving urticaria and a sensation of itch, although more severe allergic reactions are possible. The testing will be performed by specialists who are trained and experienced in the conduct and management of skin testing, and who will treat any symptoms which occur in line with local and national guidance. The patient will be contacted between 48 h and one week following testing to check whether any of the test sites developed localised redness or swelling, which indicates a possible delayed-type allergic reaction. In line with standard drug allergy testing procedure, patients may be offered a drug provocation test, whereby they are given small doses of sugammadex in a carefully monitored setting at the earliest practical opportunity. This is both for future safety of the patient and to understand the specificity of skin testing.

## Process evaluation

A process evaluation (PE) will be undertaken within the SINFONIA trial, led by collaborators at Queen’s University Belfast. It is likely that the complex decision-making processes around use and dose selection of neuromuscular blockade reversal agents (NMBAs) in major surgery are influenced by a range of organisational, clinician, and patient-related factors. It is important to develop a detailed understanding of these factors to explore the relationship between intervention delivery and trial outcomes. To understand this complexity and the likely variation in intervention delivery, we plan to embed a pragmatic PE within the trial to explore adherence to the intervention and the influence on patient and trial outcomes. A protocol for this process evaluation will be made available as a separate publication.

## Plans to promote participant retention and complete follow-up {18b}

Follow-up data will be collected for all randomised participants, unless they explicitly request to be withdrawn from the trial. If such a request is received, participants will be asked for consent for data collection from medical records to continue without further contact.

## Data management {19}

### Data collection

We will use a web-based Clinical Data Management System (CDMS) for data management, developed by the WCTU programming team. All specifications (i.e. database variables, validation checks, screens) will be agreed between the programmer and appropriate trial staff. Participant data will be collected in accordance with the protocol. Clinical data will be collected during the hospital stay up to 30 days after surgery, and thereafter from contact with the patients and their clinical teams up to 180 days. The case report forms (CRF) will be developed by the WCTU and made available to the participating sites as paper and electronic CRFs (eCRF) for ease of data collection. The trial will be conducted in accordance with the current approved protocol, Good Clinical Practice (GCP), relevant data protection regulations, the trial Data Management Plan, and standard operating procedures (SOPs). A monitoring plan and risk assessment will be devised to protect participant safety and the integrity of trial data.

### Data checks and validations

Input fields in the CDMS will be assigned validation rules as appropriate to prevent erroneous data being saved back to the database. Forms can only be saved once all input fields pass the validation rule checks. All validation rules will be documented in a Functional Requirement Specification. The trial team will implement processes to conduct manual checks on data entered by participating sites to maximise completion and accuracy of data collected. Data checking processes will be documented according to a trial-specific Data Management Plan which will be developed between the trial team, Chief Investigator, statisticians, health economists, and quality assurance staff.

### Data storage

All essential documentation and trial records will be stored by WCTU in conformance with the applicable regulatory requirements and access to stored information will be restricted to authorised personnel. Any paper data forms will be stored in a lockable filing cabinet in a secure room, to which access is restricted to authorised personnel. Electronic data will be stored in a secure area of the computer with access restricted to staff working on the trial and the WCTU Quality Assurance team. All databases containing identifiable information will be encrypted and password protected. Any data that are transferred out of the secure environment will adhere to Warwick SOPs.

### Data access and quality assurance

All data access will be controlled by individual usernames and passwords, and any changes to data will require the user to enter their username and password as an electronic signature in accordance with regulatory requirements. Staff will have access restricted to the functionality and data that are appropriate for their role in the trial and will not share their log in details.

### Archiving

Trial documentation and data will be archived for at least ten years after completion of the trial. Trial Master File and associated data will be archived by WCTU; trial data generated at sites will be archived for a minimum of 10 years and in accordance with local policy.

## Confidentiality {27}

The trial complies with all applicable UK legislation and WCTU Standard Operating Procedures. All data are being stored securely and held in accordance with the UK General Data Protection Regulations. All CRFs, questionnaires, trial reports, and communication regarding the trial will identify the participants by the assigned unique trial identifier only. Participant confidentiality will be maintained at every stage, and identifiable information will not be made publicly available to the extent permitted by the applicable laws and regulations. Personally identifiable data will not be transferred outside of the participating site other than (a) where contact details (email or postal address) have been voluntarily provided, with consent, by the participant for the purposes of receiving notification of trial findings, or (b) for trial monitoring purposes or compliance with regulatory requirements.

